#### Lifestyle sessions

An experienced dietician and psychologist will guide 18 lifestyle sessions with a duration of 75–90 minutes. A session will consist of weighing, evaluation of the previous weeks, personalised goals and BMI-SDS curve, dietary advice usually incorporated in a game, psychological training, personalised goal setting and discussing home work. All children will receive a workbook with additional information for each lifestyle session, homework and space for individualised goal setting. All children will set at least one new personalised goal per session during the initial phase. In the follow-up phase, children will be encouraged to maintain their goals and modify goals in case of no BMI-SDS reduction. Small presents will be provided as incentives for participation and achievements. Individualised incentives will be obtained if personalised goals are reached and group incentives will be obtained in case of high participation rates and preparations for the lifestyle sessions. The dietician and psychologist will put emphasis on positive reinforcement during the lifestyle sessions.

All dietary advices are based on the Dutch dietary guidelines for children with a high body weight [60] and modelled after the work of Dutch programs to prevent childhood obesity, Realfit and Slimkids [61]. During the sessions, children will follow 3 basic dietary guidelines: 1. healthy food choice, 2. regular eating pattern, and 3. normalised portion sizes. Other dietary themes that will be dealt with during the lifestyle sessions are among others: energy balance, fruit and vegetable intake, mindful eating, finding social support, trying new food items (including 2 taste session sessions) inspecting food labels and, if applicable, alcoholic beverages. Special attention will be paid to emotional eating, body dissatisfaction and disordered eating. Also, children will regularly comment on their own and other’s dietary journals. If children have not reduced their BMI-SDS after 6 lifestyle sessions, the dietician will provide the children with a personalised balanced hypo caloric diet with low-fat, nutrient dense foods of moderate proportion sizes. The diet will consist of a caloric restriction of 15% less than required [62]. Participants and parents will be guided and encouraged by the dietician to follow the hypo caloric diet and to adjust the diet with the nutritional knowledge they have gained during the previous sessions.

The psychologist will teach cognitive behavioural techniques. Children will learn how to identify, challenge and change dysfunctional cognitions about weight/obesity, food/eating, bullying, self-esteem, sedentary behaviour and physical activity by means of background information and homework assignments including ‘thought diaries’. Other themes on which the psychologist will focus are motivation monitoring, stimulus control, recognizing emotions and social skills. Children will be taught how to cope with real-life situations such as holidays, parties, celebrations, and restaurants. During the follow-up phase a relapse prevention schedule will be made by all participants. The cognitive behaviour protocols were modelled after the work of Werrij et al. [63,64].

The dietician and psychologist will guide participants to decrease sedentary behaviour. Children will be motivated to reach the advised daily 60 minutes of moderate to vigorous physical activity and to perform exhaustive physical activity for 20 minutes at least 3 days per week. Main themes to be discussed are screen time, active transportation ways and daily activity patterns.

#### Parental sessions

Parents will follow 10 parental sessions of 60 minutes guided by the dietician and psychologist who also guide the lifestyle sessions. A parental session will consist of an evaluation of the prior period, summarising the content of children’s lifestyle sessions, dietary or psychological information and goal setting. The parents will receive a workbook including background information, healthy recipes and sport facilities in their residence. The dietary information will consist of standard nutritional education that is also taught to the children. In addition, advices are given about healthy cooking habits, preparing healthy snacks for children and visibility of (un)healthy food at home. The psychologist will focus on parental techniques such as positive rewarding, managing problem behaviours and modelling behaviour of the parents. Emphasis will be put on the importance of individual incentives if children reach their personalised learning goals.

#### Individual counselling sessions

In addition to the lifestyle sessions, children will receive individualised counselling sessions. The individualised counselling sessions will be guided by either the dietician or the psychologist, dependent on the needs of the child. The individualised counselling sessions will focus on the learning goals, motivational problems, personal barriers for maintaining the leaning goals and possible depressive symptoms. Children aged 6–11 years always attend the individual sessions accompanied by a parent. Older children will be accompanied by a parent if one of the parties (e.g. dietician, psychologist, child or parents) deems a parental visit beneficial. If the child still experiences severe problems with weight reduction despite the regular lifestyle sessions and individual consults, the dietician or psychologist will schedule extra telephonic consults with the child and/or parent.

### Statistics

#### Sample size calculation

Earlier studies on weight loss in asthmatic adults demonstrated improvements in FEV_1_ of 8% and 6% respectively [65,66]. In adolescents with asthma, improvements in FEV_1_ of up to 24% were found after a weight reduction program [67]. In total, 104 participants are sufficient to detect a change of 5% in FEV_1_%, assuming a five-repeated measurement design of Hedeker et al., a two-sided alpha of 5%, a correlation between measurements of 0.7, a power of 80%, a sample size ratio of 1:1, a drop-out rate of 5% and an autoregressive(1) variance-covariance matrix structure [68].

According to the Fleisch method of power calculation, 80 participants are sufficient to detect a clinical relevant decrease of 0.25 BMI-SDS, with a two-sided alpha of 0.05, a drop-out rate of 20% and a power of 90% [69].

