**Figure 1 F1:**
[figure not shown]
**Flow diagram study design.** Abbreviations: BHR = Bronchial Hyper-Responsiveness, BMI = Body Mass index, EBC = Exhaled Breath Condensate, FeNO = Fractional exhaled Nitric Oxide, VO_2max_ = Maximal Oxygen Uptake.

Regular measurements including lung function outcomes, anthropometric outcomes, inflammatory outcomes and intervention mediators and moderators will be performed at baseline (T=0), after 6 months (T=6), 12 months (T=12) and at the end of the intervention (T=18). Every 3 months, participants will receive various questionnaires (Table 1). All procedures and materials are approved by the Medical Ethic Committee of Maastricht (MEC 09-2-088).

**Table 1 T1:** Overview of measurements per visit

	**Baseline**	**T3**	**T6**	**T9**	**T12**	**T15**	**T18**

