**Lung function parameters**							
MEFV curves: FEV_1_, FVC, FEV_1_/FVC, PEF, MEF_50_ (absolute and %predicted values)^*^	X		X		X		X
Static lung function test: TLC, RV, FRC, ERV	X						X
BHR	X						
Maximum Ergometry test: VO_2max,_ HR_max_, %fall in FEV_1_	X						X

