### Eligibility criteria

All children with asthma and overweight, aged 6–16 year, living in Southern Limburg will be invited to participate. Overweight will be defined as a BMI-SDS >1 according to the Lambda Mu and Sigma (LMS) method of Cole et al. [20] based on the reference charts of the Dutch fourth Nationwide Growth Study [21]. During the screening visit, participants will undergo lung function measurements to verify the diagnosis of asthma. A child will be considered asthmatic if at least 2 of the 3 following criteria are fulfilled: 1. asthmatic symptoms in the previous 12 months based on the International Study of Asthma and Allergy in childhood (ISAAC) questionnaire [22]; 2. use of Short Acting Beta2agonists (SABA), Long Acting Beta2agonists (LABA) or Inhaled Corticosteroids (ICS) in the previous 6 months; 3. reversibility; defined as an increase of ≥9% of the predictive value of the FEV_1_ after inhalation of 400 μg Airomir (Teva Pharma, Leiden, the Netherlands) or a positive BHR test; defined as a histamine concentration of ≤8 mg/ml necessary to provoke a drop of 20% in FEV_1_.

Children will be excluded in the case of a congenital malformation of the airways or other chronic lung diseases, syndromes accompanied by mental retardation or metabolic diseases, physical limitations to exercise, and/or a heart disease.

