#### Data analysis of primary and secondary research question

Data will be analysed by using Statistical Package for the Social Sciences (version 20.0, SPSS, Chicago, USA). Standard statistical techniques will be used for the baseline characteristics. Normal distributed variables will be expressed as means and standard deviations, non-normal distributed data will be presented as median with interquartile ranges. Multi-level analyses techniques will be used to test whether within-subject changes in FEV_1_%predicted after 18 months intervention differ between intervention and control group. Both per-protocol and intention-to-treat-analyses will be performed. The primary outcome FEV_1_%predicted will be tested two-tailed with an alpha of 5%. Correction for multiple testing will be conducted for the secondary outcomes.

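### The FEV1 sample size assumes five repeated measurements but only four are scheduled, so the stated 80% power is not that of the trial as designed

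*Protocol article*

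**What the plan says.** The sample size section of the protocol article reads: "In total, 104 participants are sufficient to detect a change of 5% in FEV_1_%, assuming a five-repeated measurement design". The other inputs it lists are two-sided alpha 5%, power 80%, correlation 0.7, an autoregressive(1) covariance structure, 1:1 allocation and 5% drop-out.

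The study design section says that the regular measurements, lung function among them, "will be performed at baseline (T=0), after 6 months (T=6), 12 months (T=12) and at the end of the intervention (T=18"). In Table 1 the spirometry row, "MEFV curves: FEV_1_, FVC, FEV_1_/FVC, PEF, MEF_50_ (absolute and %predicted values"), is marked at Baseline, T6, T12 and T18, and is blank at T3, T9 and T15.

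The data analysis section plans multi-level models to "test whether within-subject changes in FEV_1_%predicted after 18 months intervention differ between intervention and control group".

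**The concern.** The number of measurements enters a repeated-measures sample size directly, together with the correlation structure. Here it disagrees with the visit schedule in the same article.

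FEV1 % predicted is a primary outcome, and its 104 is the recruitment target, since the BMI-SDS calculation needs only 80. The 80% is also the figure against which an inconclusive FEV1 result would be read. If it belongs to another design, the reader does not know what the trial could detect.

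**Working it through.** **Is there a fifth FEV1 time point?** The candidates in the article are these.

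- Screening: "During the screening visit, participants will undergo lung function measurements to verify the diagnosis of asthma". Table 1 has no separate screening column, and the histamine test used for eligibility is marked only under Baseline, so screening and baseline appear to be one assessment.
- Readings before and after the bronchodilator are taken within a visit, so they add no time point.
- Spirometry around the exercise test is taken at Baseline and T18, which are already counted.

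I find no fifth time point in the text or in Table 1. Figure 1 was not visible to me.

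**Inputs stated in the article.** N = 104, 1:1, 5% drop-out, effect 5 points, two-sided alpha 5%, power 80%, correlation 0.7 with AR(1). Evaluable children per arm: n = 104 × 0.95 / 2 = 49.4.

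**Inputs not stated, so assumed.** These are the SD of FEV1 % predicted, the contrast, the time course of the 5-point effect, and the spacing to which 0.7 refers. I back-solve the SD and vary the rest.

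**Formula.** For a contrast c and a between-arm effect profile that reaches 5 points, let f be the variance of the estimated 5-point effect for one child, in units of SD². Then

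n = 2 (1.960 + 0.8416)² × f × SD² / 5².

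**The plan's own figure.** Setting n = 49.4 gives f × SD² = 49.4 × 25 / (2 × 7.849) = 78.67. So 104 is reproduced with five measurements if SD = √(78.67 / f₅). The implied SD depends on the contrast. Because it is unstated, 104 can be neither confirmed nor refuted.

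**Four visits, same SD and same N.** The SD cancels:

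power = Φ(2.8016 × √(f₅ / f₄) − 1.960); N for 80% = 104 × f₄ / f₅.

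There are two readings of the correlation. (a) 0.7 holds between adjacent visits whatever their spacing, so it also holds at six months. (b) 0.7 held between adjacent visits when five equally spaced visits covered the 18 months. Adjacent visits among four are then further apart, with correlation 0.7^(4/3) = 0.62.

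| Contrast | f₅ | implied SD | f₄ (a) | power (a) | N for 80% (a) | f₄ (b) | power (b) |
|---|---|---|---|---|---|---|---|
| Average over all visits | 0.6157 | 11.3 | 0.6779 | 76.1% | about 115 | 0.6097 | 80.4% |
| Average of post-baseline visits | 0.6779 | 10.8 | 0.7533 | 75.7% | about 116 | 0.6954 | 79.0% |
| Post-baseline average minus baseline | 0.7913 | 10.0 | 0.7313 | 83.0% | about 96 | 0.8635 | 76.5% |
| Linear trend reaching 5 points at T18 | 1.5928 | 7.0 | 1.3451 | 86.2% | about 88 | 1.5532 | 81.0% |
| T18 minus T0 | 1.5198 | 7.2 | 1.3140 | 85.4% | about 90 | 1.5198 | 80.0% |
| Constant post-baseline effect, conditional on baseline | 0.4016 | 14.0 | 0.4322 | 77.1% | about 112 | 0.4770 | 72.9% |

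Worked example, first row, reading (a): √(0.6157 / 0.6779) = 0.953; 2.8016 × 0.953 = 2.670; Φ(2.670 − 1.960) = 76.1%. The difference detectable with 80% power is 5 / 0.953 = 5.25 points.

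Worked example, T18 minus T0, reading (a): f₅ = 2(1 − 0.7⁴) = 1.5198 and f₄ = 2(1 − 0.7³) = 1.314. Power rises because the two end visits are three lags apart instead of four, and so are more strongly correlated.

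Across the table, power runs from 72.9% to 86.2%.

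**The case against.** The strongest objection is that the mismatch may cost nothing. The analysis section tests within-subject change after 18 months. For the contrasts closest to that, T18 minus T0 and linear trend, four visits give the same power or more: 80-81% under reading (b) and 85-86% under reading (a). This stands, and it means no loss of power can be claimed.

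A second objection is that a journal article may leave the SD and the contrast to the full protocol. That also stands, and their absence is not the point here. The number of measurements is different: the article states it, and its own schedule contradicts it.

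A reader might go further and infer that the trial is badly underpowered. Taking the SD of 11.3 implied by an average over five visits and applying it to an 18-month change score gives 48% power. The article does not support that inference. The SD is back-solved from one assumed contrast and then used for another, and the same change score with five measurements gives only 43%. The low figure therefore comes from mixing contrasts and has nothing to do with five versus four visits. Nor does the article say that the planned change will be adjusted for baseline, so power for that analysis cannot be presented as the trial's own.

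**Conclusion.** The contradiction is real. The calculation uses five measurements, the schedule has four, and the stated 80% cannot be attributed to the trial as scheduled. At 104 children, power with four visits is roughly 73% to 86%. That range assumes the 80% was correct for five measurements, AR(1) correlation with 0.7 between adjacent visits, 5% drop-out in each arm, and a normal approximation. Where the trial falls within it depends on the contrast and on the spacing to which 0.7 refers, and the article settles neither. The direction of the error is undetermined and underpowering is not shown.

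This should be fixed because the figure sets the recruitment target and frames how the primary result is read. It does not affect the validity of the treatment comparison.

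**What to change.** Redo the FEV1 calculation for the four scheduled visits and for the quantity the analysis section tests, the between-arm difference in within-subject change at 18 months. As part of that recalculation, give the SD of FEV1 % predicted and say which visit spacing the 0.7 refers to. Then restate the power, or the difference detectable with 80% power, for 104 children. If a fifth FEV1 measurement does exist, name it in the text and in Table 1 instead.

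The cost is one recalculation and a sentence or two of text. No visits or participants need be added. The restated figure may be higher or lower than 80%.

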#### Data analysis of primary and secondary research question

Data will be analysed by using Statistical Package for the Social Sciences (version 20.0, SPSS, Chicago, USA). Standard statistical techniques will be used for the baseline characteristics. Normal distributed variables will be expressed as means and standard deviations, non-normal distributed data will be presented as median with interquartile ranges. Multi-level analyses techniques will be used to test whether within-subject changes in FEV_1_%predicted after 18 months intervention differ between intervention and control group. Both per-protocol and intention-to-treat-analyses will be performed. The primary outcome FEV_1_%predicted will be tested two-tailed with an alpha of 5%. Correction for multiple testing will be conducted for the secondary outcomes.

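### The primary FEV1 test is framed as a comparison of change with no stated baseline adjustment; adjusting would cut the variance of the 18-month contrast by about a third under AR(1) 0.7 on the four-visit schedule

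*Protocol article*

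**What the plan says.** The section on data analysis of the primary and secondary research question defines the primary test in one sentence: "Multi-level analyses techniques will be used to test whether within-subject changes in FEV_1_%predicted after 18 months intervention differ between intervention and control group". The test is two-sided at 5%. The section names no fixed effects, covariates or constraint on the baseline means. It gives no model for BMI-SDS, the other primary outcome.

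The sample size section states that "104 participants are sufficient to detect a change of 5% in FEV_1" %, "assuming a five-repeated measurement design of Hedeker et al", with "a correlation between measurements of 0.7" and "an autoregressive(1) variance-covariance matrix structure". It also assumes 80% power, 1:1 allocation and 5% dropout. It gives no SD for FEV1 %predicted.

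The Table 1 row "MEFV curves: FEV_1_, FVC, FEV_1_/FVC, PEF, MEF_50_ (absolute and %predicted values") is marked at baseline, T6, T12 and T18: four occasions, not five.

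**The concern.** Read naturally, a test of whether within-subject change differs between arms is a group-by-time or change-score contrast in which each arm keeps its own baseline mean. Such a contrast subtracts the baseline in full, whatever its correlation with the outcome. When that correlation is modest, full subtraction adds noise. Below a correlation of 0.5, the change is more variable than the 18-month value alone.

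The plan's own planning assumption is a correlation that decays over visits, so this applies here. What is at stake is precision in a trial of 104 children. The baseline value that would recover the precision is already being collected.

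**Working it through.** **Inputs.** Correlation 0.7, AR(1), five measurements, N = 104, difference of 5, two-sided 5%, 80% power and 5% dropout (sample size section); four FEV1 visits at 0, 6, 12 and 18 months (study design section and Table 1). The SD is not stated.

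**The plan's own figure.** N = 104 can be neither reproduced nor refuted without an SD. Solving backwards, it implies an SD of about 6.5 to 7.9 for an endpoint-change or linear-trend contrast, 8.2 to 9.1 for the final value alone, and 10.2 to 11.6 for a time-averaged effect. The ranges cover four or five measurements and different ways of applying dropout. The comparison below does not need the SD, because it cancels.

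**Formulas.** Let r be the correlation between baseline and the 18-month value, with equal variances. Per child, in units of SD²:

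- change from baseline: 2(1 − r)
- baseline-adjusted: 1 − r²
- ratio, adjusted to change: (1 + r)/2
- power of the adjusted test where the change test has 80%: Φ(2.8016/√ratio − 1.96), with 2.8016 = 1.9600 + 0.8416

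**Results.**

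| Reading of 0.7 | r | Change | Adjusted | Ratio | Variance saved | SE reduction | 80% becomes |
|---|---|---|---|---|---|---|---|
| AR(1), four visits | 0.7³ = 0.343 | 1.314 | 0.882 | 0.672 | 33% | 18% | 93% |
| AR(1), five measurements | 0.7⁴ = 0.240 | 1.520 | 0.942 | 0.620 | 38% | 21% | 94% |
| 0.7 is the baseline-to-T18 correlation | 0.700 | 0.600 | 0.510 | 0.850 | 15% | 8% | 86% |

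In both AR(1) rows the change variance exceeds 1.000, the variance of the 18-month value alone.

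**The same result in participants.** Suppose the change test has exactly 80% power with 104 children, so 52 × 0.95 = 49.4 evaluable per arm. The adjusted test needs:

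- four visits: 49.4 × 0.672 = 33.2, so 34 per arm; 68/0.95 gives 72 in total
- five measurements: 49.4 × 0.620 = 30.6, so 31 per arm; 62/0.95 gives 66
- r = 0.7: 49.4 × 0.85 = 42.0, so 42 per arm; 84/0.95 gives 89

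These cases correspond to SDs of about 7.7, 7.2 and 11.5. Those SDs are back-solved, not stated in the plan.

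**Do the intermediate visits recover the loss?** No. Generalised least squares with complete data and AR(1) 0.7, comparing a common baseline mean with free baseline means, gives variance ratios of 0.672 (four visits) and 0.620 (five) for saturated visit means. For a linear group-by-time slope the ratios are 0.666 and 0.607. A multi-level model with free baseline means carries the same loss as a simple change score.

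**The case against.** The strongest reply is that the sentence does not exclude adjustment. A mixed model with equal baseline means is a multi-level model, and its arm difference at 18 months is a between-arm difference in change. A journal article commonly leaves covariates to the full protocol or analysis plan. A reader might infer that the authors chose change scores in place of adjustment, but the text neither includes nor rules out adjustment. This part of the reply stands, and the point is therefore conditional on how the model is fitted. It does not remove the point: the article does fix the primary contrast, frames it as change, and gives no sign of adjustment.

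A second reply is that the size depends on a planning assumption. This also stands. The article does not say whether 0.7 applies to adjacent visits or to all pairs, and AR(1) is not stated as the analysis model. The five-measurement assumption also disagrees with the four scheduled visits. One third is therefore not an upper limit, and 15% is not a lower one: an assumed correlation of 0.9 would leave a saving of 5%. The direction is the same under every reading.

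Third, the change comparison is unbiased under randomisation and its type I error is valid. This stands in full. A chance baseline imbalance affects the precision of a particular estimate, not the validity of the test.

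**Conclusion.** The point holds as a matter of efficiency. If the primary test is run with baseline means free in each arm, it gives up about 33% in variance (18% in standard error) under AR(1) 0.7 on the four-visit schedule. The loss is 38% with five measurements, and 15% if 0.7 is the baseline-to-18-month correlation. These figures assume equal variances over time and complete data.

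A reader might go further and conclude that the trial is underpowered or that N = 104 is wrong. The documents do not support that. Without an SD the actual power is unknown, and the 93%, 94% and 86% show only what adjustment would do to a change test that starts at exactly 80%. Nor is there ground for calling the stated test biased or invalid. This is an improvement available at no data cost, not the correction of an invalid analysis.

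**What to change.** Add one sentence to the data analysis section: the primary multi-level model uses FEV1 %predicted at T0, T6, T12 and T18 with visit as a category, constrains the baseline mean to be equal in the two arms, includes arm-by-visit effects after baseline, and takes the arm difference at T18 as the primary estimate. Equivalently, use baseline FEV1 %predicted as a covariate, with T6, T12 and T18 as the outcomes.

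Either form requires a baseline value that allocation cannot have affected. The article points that way: bronchial hyper-responsiveness is scheduled only at baseline in Table 1 and is also part of eligibility, which is settled before randomisation. The sentence could confirm this for FEV1.

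The same approach could be offered for BMI-SDS as a suggestion only, because the article does not state how that outcome will be analysed.

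The cost is wording: no new data, visits or participants.

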**Methods/design:**

The Mikado study is a two-armed, randomised controlled trial. In total, 104 participants will be recruited via online questionnaires, pulmonary paediatricians, the youth department of the Municipal Health Services and cohorts of existing studies. All participants will be aged 6–16 years, will have current asthma, a Body Mass Index in the overweight or obesity range, and no serious comorbidities (such as diabetes, heart diseases). Participants in the intervention arm will receive a multifactorial intervention of 18 months consisting of sessions concerning sports, parental involvement, individual counselling and lifestyle advices including dietary advices and cognitive behavioural therapy. The control group will receive usual care. The primary outcome variables will include Forced Expiratory Volume in one second and Body Mass Index - Standard Deviation Score. Secondary outcomes will include other lung function parameters (including dynamic and static lung function parameters), asthma control, asthma-specific quality of life, use of asthma medication and markers of systemic inflammation and airway inflammation.

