### The primary research question is

What are the effects of an 18-month multifactorial intervention on FEV_1_%predicted and BMI-SDS?

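### BMI-SDS is primary in the abstract and the research question but not in the analysis section, and no rule controls error across two primaries

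*Protocol article*

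**What the plan says.** Four places in the protocol article bear on this.

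- Abstract, Methods/design: "The primary outcome variables will include Forced Expiratory Volume in one second and Body Mass Index - Standard Deviation Score". Two outcomes are named, in the plural.
- The primary research question: "What are the effects of an 18-month multifactorial intervention on FEV_1_%predicted and BMI-SDS". Both outcomes again, with no order and no statement on whether one or both must improve.
- Sample size calculation: one calculation per outcome. For FEV1, "In total, 104 participants are sufficient to detect a change of 5% in FEV_1"%, at two-sided 5% and 80% power. For BMI-SDS, 80 participants to detect a decrease of 0.25, "with a two-sided alpha of 0.05, a drop-out rate of 20% and a power of 90" per cent. Each uses the whole 5%.
- Data analysis of primary and secondary research question: "The primary outcome FEV_1_%predicted will be tested two-tailed with an alpha of 5" per cent, in the singular. The named model is also for FEV1: "Multi-level analyses techniques will be used to test whether within-subject changes in FEV_1_%predicted after 18 months intervention differ between intervention and control group". On multiplicity: "Correction for multiple testing will be conducted for the secondary outcomes". BMI-SDS is not mentioned in this section.

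**The concern.** No single reading fits all four places. If BMI-SDS is primary, the analysis section is wrong to speak of one primary outcome, and its correction for secondary outcomes does not reach the second primary. If BMI-SDS is secondary, the abstract and the primary research question are wrong.

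The case where the two readings part is a plausible one. The programme acts on weight directly, so BMI-SDS could fall while FEV1 %predicted does not change. Under the abstract and research question, that could be reported as an effect on a primary outcome. Under the analysis section, the primary test has failed. The Discussion says that a programme proven effective should enter the childhood asthma guidelines, so what counts as proof should be settled before the data are seen.

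**Working it through.** **Inputs from the article.** Two-sided alpha 0.05 for FEV1 (sample size and analysis sections) and 0.05 for BMI-SDS (sample size section only). FEV1: N = 104, power 80%. BMI-SDS: N = 80, power 90%.

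**The plan's own figure.** With FEV1 %predicted as the only primary test, the type I error is 5%, as stated. The sample sizes 104 and 80 cannot be reproduced because the article gives no standard deviation. They are taken as given, and the scaling below does not need one.

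**Error if either outcome sufficed (a rule the article does not state).** The critical value is 1.960 for each test.

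- Independent tests: 1 − (1 − 0.05)² = 1 − 0.9025 = 0.0975.
- Upper bound whatever the dependence: 0.05 + 0.05 = 0.10.
- Correlated tests: 1 − P(|Z1| ≤ 1.960 and |Z2| ≤ 1.960), bivariate normal. The article gives no correlation, so a range is shown.

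| Assumed test correlation | Family-wise error |
|---|---|
| 0 | 9.75% |
| 0.3 | 9.5% |
| 0.5 | 9.1% |
| 0.7 | 8.3% |
| 0.9 | 7.0% |

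**Error under other rules.**

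- FEV1 sole primary: 5%.
- Fixed sequence, FEV1 then BMI-SDS, each at 5%: if the FEV1 null is true, any false claim must begin with a false FEV1 rejection, which has probability 5%. If only the BMI-SDS null is true, a false claim needs a false BMI-SDS rejection, at most 5%. So the error is at most 5%.
- Both required: a false claim of joint success needs at least one true null to be rejected, so at most 5%.

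**Cost of an equal split (0.025 each).** Normal quantiles: 1.960 for two-sided 0.05, 2.241 for two-sided 0.025, 0.842 for 80% power, 1.282 for 90% power.

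- FEV1 power at N = 104: Φ(1.960 + 0.842 − 2.241) = Φ(0.560) = 71.2%.
- N to restore 80% for FEV1: 104 × [(2.241 + 0.842)/(1.960 + 0.842)]² = 104 × 1.211 = 125.9, so 126.
- N for 90% on BMI-SDS: 80 × [(2.241 + 1.282)/(1.960 + 1.282)]² = 94.5, so 95. This is still within 104.

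**Cost of the fixed sequence.** FEV1 keeps 5% and its planned 80%. BMI-SDS at N = 104 and 5%, with its own planning assumptions, has power Φ[(1.960 + 1.282) × √(104/80) − 1.960] = Φ(1.736) = 95.9%. Tested only after FEV1 succeeds, its chance of a confirmatory claim is 0.80 × 0.959 = 76.7% if the two tests are independent.

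**The case against.** The strongest reply is that the analysis section gives one decisive test, with its model, sidedness and alpha, and that this test has a 5% error. Nowhere does the article say that success on either outcome is enough. This stands. A reader might infer from two primaries at 5% each that the trial's error is 9.75%, but that needs a win rule which the article does not contain. What is shown is an undefined success rule, not an established inflation.

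A reader might also infer that BMI-SDS has no error control of any kind. The article does not support this either. The sample size section assigns it a two-sided 5%, and if it is really secondary the stated correction covers it. What is missing is a settled status and, if it is primary, control across the pair.

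A third tempting reading is that two analysis populations double the routes to success. The article says only "Both per-protocol and intention-to-treat-analyses will be performed". It does not call them equal or let either one carry the claim. Which population decides, and which model BMI-SDS receives, are details that a journal article may leave to the full protocol or analysis plan.

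Finally, one can object to putting FEV1 first. BMI-SDS is planned at the higher power, and the objective presents asthma benefit alongside weight reduction, so BMI-SDS first, or both required, would be coherent too. Either would remove the ambiguity. FEV1 first is preferred only because the analysis section already gives it priority.

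None of these replies makes the four sections agree. A separate analysis plan could choose a reading, but the article would still contradict itself.

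**Conclusion.** The point holds as an internal contradiction about the status of BMI-SDS. It is primary in the abstract and the primary research question, is sized at a full two-sided 5%, and is absent from an analysis section that names FEV1 %predicted as the only primary outcome and corrects only secondary ones. If BMI-SDS is primary, error across the two primaries is uncontrolled.

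The numerical consequence is conditional. Only if either outcome sufficed would family-wise error be about 7.0% to 9.75%, for assumed test correlations from 0.9 down to 0. Under the other three rules examined it is at most 5%. The power figures rest on the article's stated sample sizes and powers, which could not be reproduced, and the 76.7% also assumes independent tests.

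**What to change.** State the status of BMI-SDS once and align the abstract, the primary research question, the sample size section and the analysis section with it. The recommended rule is a fixed sequence: test FEV1 %predicted at two-sided 5%, then test BMI-SDS at two-sided 5% only if FEV1 is significant.

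This takes a few sentences, leaves N at 104 and keeps FEV1 power at its planned 80%. An equal alpha split would lower that to about 71%, or require about 126 participants. The price of the sequence is that a BMI-SDS effect could be reported only as non-confirmatory if FEV1 fails.

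An acceptable alternative is to declare BMI-SDS secondary, under the correction already promised, and to amend the abstract and research question accordingly. Naming intention-to-treat as the deciding analysis would be a reasonable clarification in the same edit, but it is not part of this error.
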